# The effectiveness of the use of a digital activity coaching system in addition to a two-week home-based exercise program in patients after total knee arthroplasty: study protocol for a randomized controlled trial

**DOI:** 10.1186/s12891-017-1647-5

**Published:** 2017-07-05

**Keywords:** Accelerometer, Home-based exercise program, Total knee arthroplasty, Physical therapy

## Abstract

**Background:**

There is consistent evidence that supervised programs are not superior to home-based programs after total knee arthroplasty (TKA), especially in patients without complications. Home-based exercise programs are effective, but we hypothesize that their effectiveness can be improved by increasing the adherence to physical therapy advice to reach an adequate exercise level during the program and thereafter. Our hypothesis is that an activity coaching system (accelerometer-based activity sensor), alongside a home-based exercise program, will increase adherence to exercises and the activity level, thereby improving physical functioning and recovery. The objective of this study is to determine the effectiveness of an activity coaching system in addition to a home-based exercise program after a TKA compared to only the home-based exercise program with physical functioning as outcome.

**Methods:**

This study is a single-blind randomized controlled trial. Both the intervention (*n* = 55) and the control group (*n* = 55) receive a two-week home-based exercise program, and the intervention group receives an additional activity coaching system. This is a hand-held electronic device together with an app on a smartphone providing information and advice on exercise behavior during the day. The primary outcome is physical functioning, measured with the Timed Up and Go test (TUG) after two weeks, six weeks and three months. Secondary outcomes are 1) adherence to the activity level (activity diary); 2) physical functioning, measured with the 2-Minute Walk Test (2MWT) and the Knee Osteoarthritis Outcome Score; 3) quality of life (SF-36); 4) healthcare use up to one year postoperatively and 5) cost-effectiveness. Data are collected preoperatively, three days, two and six weeks, three months and one year postoperatively.

**Discussion:**

The strengths of the study are the use of both performance-based tests and self-reported questionnaires and the personalized tailored program after TKA given by specialized physical therapists. Its weakness is the lack of blinding of the participants to treatment allocation. Outcomes are generalizable to uncomplicated patients as defined in the inclusion criteria.

**Trial registration:**

The trial is registered in the Dutch Trial Register (www.trialregister.nl, NTR 5109) (March 22, 2015).

## Background

An increasing number of people have some degree of knee pain and functional limitations associated with radiographic evidence of osteoarthritis. Osteoarthritis is associated with pain, stiffness and impairments in activities of daily living [1]. When conservative treatment options, like physical therapy, losing weight, nonsteroidal anti-inflammatory drugs (NSAIDs) and intra-articular injections, are not effective anymore, a total knee arthroplasty (TKA) may be indicated [2]. The number of TKA procedures performed annually is expected to increase due to demographic and anthropometric factors like the ageing population and the increasing incidence of obesity [3]. In the Netherlands, for instance, with a population of 17 million, the number of TKA procedures was about 24,000 in 2013 whereas this figure is expected to rise to 58,000 per year in 2030 [3]. Postoperative physical therapy is the usual care after TKA [4], but there is inconsistent evidence about the effectiveness of physical therapy after TKA [5, 6]. A recent systematic review showed that physical therapy is not very effective in the long term after a TKA in terms of physical function and pain [5]. However, the physical therapy interventions as described in this review consisted of a variety of physical therapy programs such as pool- and gym-based exercises, walking skills and additional balance training or ergometer cycling. However, this review did not study the potentially important role of treatment adherence and did not include studies about home-based exercise programs after TKA. A systematic review by Coppola [7] specifically focused on a comparison between physical therapy and unsupervised home exercise in post-surgical knee disorders. Ten randomized controlled trials (RCTs) were included in this review. In a young and healthy population without comorbidities, supervised physical therapy is not more beneficial than a home-based exercise program following relatively simple knee surgical procedures (such as arthroscopic meniscectomy). There is also consistent evidence that supervised programs are not superior to home-based programs in uncomplicated patients after TKA [8–13]. Important success factors for home-based programs include the adequate patients with a favourable prognosis and increasing the adherence to the program, for instance by telerehabilitation. Tousignant et al. [12] compared the effectiveness of home telerehabilitation with conventional rehabilitation following TKA in a randomized controlled trial. In this study, home telerehabilitation seems at least as effective as conventional rehabilitation. We hypothesize that not all patients will benefit from home-based exercise programs because patients with a worse prognosis need more adapted exercise protocols and hands-on physical therapy support. Over the last few years prognostic factors in relation to TKA have been studied. The risk factors associated with worse outcome are older age [14, 15], obesity [16], worse preoperative physical status [17, 18], more comorbidities [17, 19], lack of self-efficacy [20] and psychological distress [20, 21]. Patients with a good prognosis (active coping and better preoperative functional status measured with the Timed Up and Go test (TUG) and 6-Minute Walk Test (6MWT) [22] probably do not need intensive care from the physical therapists. Possibly, these patients will benefit from a home-based exercise program only. However, adherence to such a program seems pivotal in terms of having an impact. Improvement in pain relief and clinical outcomes in patients with osteoarthritis is largely dependent on intervention adherence [23]. Exercise adherence rates are low in patients with osteoarthritis and arthritis, varying from 53.2 [24] to 70% [25]. Adherence rates were generally higher in supervised programs [26]. Adherence may be improved by an accelerometer-based activity sensor, which provides feedback on the activity level (type of activities performed and the time spent on it). To increase the adherence and thereby improve recovery after TKA we aim to study the effect of the additional use of such an activity coaching system alongside a home-based exercise program. This activity coaching system showed positive results in a pilot study of chronic obstructive pulmonary disease (COPD) patients [27]. The patients were randomly assigned to the activity coaching system or usual care group, and those in the activity coaching system group showed a satisfactory adherence to exercises [27]. We hypothesize that the activity coaching system in combination with the home-based exercise program leads to better adherence and thereby better results in terms of physical functioning than the home-based exercise program in the period of two weeks to three months after TKA surgery.

### Objective

The primary objective of this study is to determine the additive effect of a digital activity coaching system being introduced alongside a home-based exercise program after a TKA on physical functioning measured with the TUG after two weeks, six weeks and three months. The secondary objectives are to determine the additive effect of a digital activity coaching system alongside a home-based exercise program on 1) adherence to the activity level (activity diary); 2) physical functioning measured with the 2-Minute Walk Test (2MWT) and self-reported physical function (Knee Osteoarthritis Outcome Score [KOOS]) at two and six weeks, three months and one year; 3) quality of life (SF-36) at two and six weeks, three months and one year; 4) healthcare use for one year after TKA and 5) cost-effectiveness.

Alongside the RCT, a process evaluation is conducted to determine the usability of the digital activity coaching system in patients after a TKA: a quantitative comparison between the activity diary and the accelerometer data, and interviews to gain insight into the experiences of patients.

## Methods

### Study design

The study design is a single-blinded parallel superiority RCT. The flow chart is shown in Fig. 1. Postoperative measurements take place at the beginning of the home-based exercise program, after two weeks, after six weeks, after three months and after one year. The outcome measures are performed by one researcher, who is blinded to the group assignment.

**Fig. 1 Fig1:**
[figure not shown]
Flow chart

### Participants

The population consists of patients receiving a TKA with relatively favourable prognosis. In this study we include patients with a good prognosis for functional recovery after TKA to guarantee that patients are able to perform an intensive two-week home-based exercise program on their own. The inclusion criteria are: 1) an adequate preoperative physical status: Bade et al. [21] showed that individuals walking <314 m on the 6-Minute Walk Test (6MWT) before surgery had the poorest physical function six months after surgery. Therefore, we include patients who can walk at least 120 m preoperatively in a 2MWT; 2) absence of compensatory movements during walking, because patients with inadequate walking patterns need more guidance from a physical therapist to relearn a normal dynamic gait (‘no’ on all 13 items of the Gait Analysis List Nijmegen (GALN); [25–27] 3) Body Mass Index (BMI) < 30, because patients with a BMI ≥ 30 kg/m are at higher risk of lower functional outcomes and of complications following primary TKA; [28] 4) age < 80 years because older age is related to worse functioning after TKA; [29] 5) ability to perform activities of daily living independently, which is a requirement for going home after a three-day hospital stay; and 6) having an active coping style as measured with the Patient Activation Measure (PAM) > 60 points. The PAM consists of 22 items. Each item is scored on a four-point Likert scale resulting in a total score range of 22–88. If patients score > 60 points [28], we hypothesize that they are able to take responsibility for their active behavior and adherence to the exercise program.

The exclusion criteria are: 1) all patients with comorbidities (such as heart or lung diseases, (orthopedic) problems in other joints, cancer and movement disorders) who need individually adapted exercise protocols; 2) severe mental disorders; 3) postoperative complications (such as open wounds, infections); 4) delay in recovery shown as >3 days staying in the hospital. All patients were recruited from the Medisch Spectrum Twente (MST) community hospital in the Netherlands.

### Procedures and informed consent

All eligible patients are informed about this study and are invited to participate by the orthopedic surgeon before surgery. The surgeon informs the researcher about patients possibly willing to participate. The researcher informs the patients by phone about the study and provides them with a patient information letter. Patients have one week to consider participating in the study. Patients who are willing to participate sign an informed consent form. After that, the researcher performs the preoperative measures and determines whether the patient is eligible. To minimize the patients’ load, the preoperative assessment is used as an inclusion criterion and preoperative measurement using overlapping tests. Five orthopedic surgeons perform the TKA surgeries. The number of TKA surgeries per year carried out by each surgeon varies from 50 to 70. After surgery, the definitive inclusion takes place if patients are going home after three days post-surgery and no complications are present. After the definitive inclusion, the baseline measurement and randomization take place. The baseline measurement is planned preferably for the third day, and at the latest for the fifth day. A flow chart is shown in Fig. 1. Subjects can leave the study at any time for any reason if they wish to do so without any consequences. The researcher will report serious adverse events to the accredited medical ethical review board of the Medisch Spectrum Twente community hospital in Enschede, the Netherlands, which approved the trial (registration number P15–09, NL52370.044.15). The researcher can decide to withdraw a patient during the study for urgent medical reasons, such as thrombosis, infections of the knee or other complications. KH is the coordinator of the trial and the other authors comprise the steering committee.

### Randomization, blinding and treatment allocation

The orthopedic surgeon checks the inclusion criteria after surgery for definitive inclusion. To assign participants to either of the groups a randomization list is generated by a computer (www.randomization.com) using block randomization with a block size of 6. Pre-stratification is applied for the level of physical activity determined with the activity coaching system prior to surgery (< the median level or ≥ the median level). The median activity level was determined in a pilot of 10 consecutive patients. An independent secretary not involved in enrolling participants in the study prepares concealed, consecutively numbered, sealed, opaque envelopes. The envelopes contain papers indicating the allocated treatment. Participants will receive their envelope at the start of the home-based exercise program from another independent secretary who is not aware of the randomization sequence. Participants can open the envelope while with the physical therapist. Subsequently, the physical therapist will inform the trial coordinator (KH) about the treatment allocation. Patients are instructed not to tell the researcher which group they are randomized to during the follow-up measurements.

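### One fixed block size of 6 per stratum at one hospital, with every allocation reported to the trial coordinator, leaves about a quarter of allocations deducible by anyone who holds the block size, the history and the strata

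*Protocol article*

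**What the plan says.** The section on randomization, blinding and treatment allocation describes a computer-generated list "using block randomization with a block size of 6". No other block size is mentioned. The list is split in two: "Pre-stratification is applied for the level of physical activity determined with the activity coaching system prior to surgery", with the cut at a median taken from a small pilot. The Participants section names a single recruiting hospital. The abstract gives equal arms: "Both the intervention (*n* = 55) and the control group (*n* = 55) receive a two-week home-based exercise program".

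Concealment is otherwise careful. One independent secretary, who has no part in enrolment, prepares numbered, sealed, opaque envelopes. A second secretary, unaware of the sequence, hands them over. The patient opens the envelope with the therapist present, and then "the physical therapist will inform the trial coordinator" which arm it was.

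On roles, the section on procedures and informed consent calls this person only the coordinator of the trial. Surgeons invite patients, and "The surgeon informs the researcher about patients possibly willing to participate". The researcher then carries out the preoperative tests and settles preoperative eligibility. After surgery the surgeon checks the criteria for definitive inclusion, and randomization follows. The Study design section adds: "The outcome measures are performed by one researcher, who is blinded to the group assignment".

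**The concern.** Opaque envelopes hide the next allocation only as long as nobody can infer it from the previous ones. A single block size lets a complete record of past allocations reveal the end of each block, and the plan builds up such a record in one person's hands during recruitment. Because there is one hospital, that record is not broken up by site.

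Definitive inclusion comes after surgery and before randomization, and part of it is a judgment about complications and discharge. If someone able to foresee the next arm could also influence that judgment, patients could be included selectively and the arms would no longer be comparable. Patients and therapists know the arm here, so concealment of the sequence and the blinding of the one outcome assessor carry much of the protection against bias. A record of individual allocations should therefore sit away from both enrolment and assessment, and the article does not say that it does.

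**Working it through.** The article gives no predictability figure, so there is none to reproduce.

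**Inputs**
- Block size 6 and two strata: section on randomization, blinding and treatment allocation.
- 1:1 allocation, 55 against 55: abstract. I take this to mean 3 + 3 in each block.
- One hospital: Participants section.
- N = 110: Sample size section.

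**Step 1. Certain allocations within one block.** There are C(6,3) = 20 equally likely balanced blocks. An allocation is certain once one arm's three places are used up.
- 4th place: the first three are all the same arm, 2/20 = 0.10.
- 5th place: the last two are the same arm, 2 × C(4,1)/20 = 8/20 = 0.40.
- 6th place: always, 1.00.

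The sum is 0.10 + 0.40 + 1.00 = 1.5 of 6, or 25%. The closed form with b = 3 agrees: 2b/(b + 1) = 6/4 = 1.5.

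**Step 2. Best guess when not certain.** Always guessing the arm that is behind gives b + 2^(2b−1)/C(2b,b) − 1/2 = 3 + 32/20 − 0.5 = 4.1 correct of 6, or 68.3%, against 50% by chance.

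**Step 3. This trial's size and strata.** Two strata leave two possibly incomplete last blocks. The stratum sizes add up to 110, which leaves remainder 2 on division by 6. The possible pairs of leftovers are therefore (0,2), (1,1), (2,0), (3,5), (4,4) and (5,3). If these are equally likely, the mean leftover is 5 patients in total, so about 105 patients sit in complete blocks: 105/6 × 1.5 = 26.25. Leftovers of 4 and 5 patients contribute 0.10 and 0.50 certain allocations, which averages 0.2 over the six pairs. The total is about 26.4 of 110, or 24.0%. A simulation of 10,000 trials gave the same 24.0% (26.4 patients), with 95% of runs between 19% and 29%. A 30:70 split of the strata made no material difference (24.0%).

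**Step 4. Without the stratum.** The same history, but with each patient's stratum unknown, gave about 0.5% certain allocations (100 simulated trials). Knowledge of the stratum is therefore decisive.

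**Step 5. Varied block sizes.** On a single list of 110, with the set of sizes known but their order unknown, certain allocations fall to about 5.6% for a random mix of 4 and 6, and to about 2.2% for 4, 6 and 8 (1,000 simulated trials each).

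**Step 6. Who could hold all three pieces.** The history goes to the coordinator by plan. The block size is very likely known to the coordinator, because the procedures section describes the steering committee as the other authors. That makes the coordinator an author of the article that prints the block size. Access to each patient's stratum is plausible but not stated.

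**The case against.** The strongest reply is that selective inclusion needs one person who both foresees the next arm and controls entry, and the article shows no such person. A reader might infer that the coordinator runs recruitment, so that a quarter of allocations become known to someone choosing patients. The text does not support this. The coordinator is named only as coordinator of the trial, while invitation, eligibility and definitive inclusion lie with the surgeons and the researcher, none of whom is said to receive allocations. The article is silent on whether coordinator and researcher are the same person, and silence is not evidence that they are.

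A reader might also infer that the coordinator's record unblinds the assessor. The Study design section states that the assessing researcher is blinded, and patients are told not to disclose their arm. A condensed article need not list every record withheld from that researcher.

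Further points stand. Most entry criteria are numerical thresholds. The researcher's eligibility decision precedes surgery, when the order in which patients will reach randomization is not yet fixed. Stratified blocks of 6 with sealed envelopes and independent secretaries are a recognised procedure. Someone must also know who has the device, because every third such patient is invited to an interview (Interviews section). The coordinator later checks those transcripts (section on healthcare costs and cost-effectiveness). Finally, recruitment was planned to end on 1 August 2017 and the article is dated 5 July 2017, so few envelopes may have been left.

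These points reduce the concern to a risk. They do not remove it: the single block size and the report to the coordinator are both stated procedure, and neither is needed for the design to work.

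**Conclusion.** The point holds as a modest, inexpensive improvement to concealment. About a quarter of allocations (roughly 24%, about 26 of 110) could be deduced in advance by anyone who holds the block size, the full history and each patient's stratum. This assumes blocks of 3 + 3 and a record kept separately by stratum. If the stratum is not known, the figure is about 0.5%. The article does not establish that the coordinator has the stratum, takes part in enrolment or shares allocations with the blinded researcher. It therefore shows neither selection bias nor unblinding, only an avoidable route to them.

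**What to change.** 1. For envelopes not yet prepared, generate the list within each stratum with randomly varied block sizes (for example 4, 6 and 8), and do not disclose the sizes while recruitment is open.
2. Have the therapist report each allocation to the independent secretary who has no part in enrolment, or to another person with no role in eligibility, inclusion or outcome measurement.
3. State that individual allocations are released only for a safety need or for a named task, such as choosing interview participants, and never to the researcher who performs the outcome measures.

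The cost is a few lines of protocol text, a new recipient for one message and a new list for the remaining envelopes. The possible final imbalance grows slightly. Half an unfinished block in each of two strata is at most 2 × 3 = 6 patients with blocks of 6, and 2 × 4 = 8 if the last blocks are of size 8. If recruitment is nearly complete, new block sizes change little. The change of recipient and the release rule can still keep individual allocations away from whoever performs the remaining follow-up measurements.

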### Home-based exercise program

Patients in the intervention group and control group both receive a home-based exercise program. A trained physical therapist experienced in the treatment of patients after TKA and trained in the home-based exercise program explains the program to the patients. There are at least two contact moments: at the start of the program, to give exercise instructions and feedback on the correct performance, and at the end of the program, to monitor the effectiveness. When in need of help the patient is allowed to consult the therapist. The program is explained face to face at the patients’ home immediately after their hospital stay and the exercises are practiced with the patient to be sure that they are done correctly. The program consists of cycling on a home trainer, outside walking and some exercises to improve range of motion (ROM) and muscle strength. The program is shown in Table 1. The home-based exercise program is followed for two weeks and patients are asked to perform the exercises at least five times a day with a gradual increase in time and speed within the two weeks. Patients receive a home trainer for two weeks to do their cycling exercises. Apart from the home-based exercise program patients are allowed to do extra walks or extra daily activities if they want and are able to do so. They are instructed to avoid strenuous activities such as playing football or other sports activities*.* Patients are informed that they can contact the physical therapist if they need consultation and are allowed to receive other kinds of care (e.g. help in the household). There is no limit on the number of consultations needed, because patients need to be sure that they do their exercise adequately. Healthcare use (including physical therapy consultations) is compared between the intervention and the control group.

**Table 1 Tab1:** exercise program

Week 1	
Day 1	• Explaining home-based exercise program through physical therapist
	• All exercises were explained
Day 2	• Cycling on a hometrainer 2 × 10 min
	• Walking outside 2 × 15 min
	• RoM exercises knee 15 min
Day 3	• Cycling on a hometrainer 2 × 10 min
	• Muscle strength exercises quadriceps 15 min
	• Walking up and down stairs 5 min
	• Walking outside 15 min
Day 4	• Hometrainer 1 × 10 min and 1 × 15 min
	• Walking outside 2 × 15 min
	• RoM exercises knee 15 min
	• Muscle strength exercises quadriceps 15 min
Day 5	• Hometrainer 1 × 10 min en 1 × 15 min • Walking outside 2 × 15 min
	• RoM exercises knee 15 min
	• Muscle strength exercises quadriceps 15 min
Day 6	• Hometrainer 2 × 15 min
	• Walking outside 2 × 15 min
	• RoM exercises knee 15 min
	• Muscle strength exercises quadriceps10 minutes
Day 7	• Hometrainer 2 × 15 min
	• Walking outside 1 × 20 min
	• RoM exercises knee 10 min
	• Muscle strength exercises quadriceps 15 min
Week 2	
Day 8	• Hometrainer 2 × 15 min
	• Walking outside 2 × 20 min
	• RoM exercises knee 15 min
	• Muscle strength exercises quadriceps 15 min
	• Walking up and down stairs 5 min
Day 9	• Hometrainer 2 × 15 min
	• Walking outside 2 × 20 min
	• RoM exercises knee 15 min
	• Muscle strength exercises quadriceps 15 min
Day 10	• Hometrainer 2 × 15 min
	• Walking outside 2 × 20 min
	• RoM exercises knee 15 min
	• Muscle strength exercises quadriceps 15 min
Day 11	• Hometrainer 2 × 20 min
	• Walking outside 1× 30 min
	• RoM exercises knee 15 min
	• Muscle strength exercises quadriceps 15 min
Day 12	• Hometrainer 2 × 20 min
	• Walking outside 1× 30 min
	• RoM exercises knee 15 min
	• Muscle strength exercises quadriceps 15 min
Day 13	• Hometrainer 2 × 20 min
	• Walking outside 2 × 30 min
	• RoM exercises knee 15 min
	• Muscle strength exercises quadriceps 15 min
Day 14	• Hometrainer 2 × 20 min
	• Walking outside 2 × 30 min
	• RoM exercises knee 15 min
	• Muscle strength exercises quadriceps 15 min

